## Abstract

*Background*. The Sanfu herbal patch (SHP) has been widely used to treat allergic rhinitis (AR) in China. SHP has been reported to be effective for managing the symptoms of AR, but the evidence suffers from methodological limitations. Therefore, we designed a three-armed, randomized, and placebo-controlled trial to evaluate the efficacy and safety of SHP for persistent allergic rhinitis (PAR). *Methods*. The trial consists of 5 treatment sessions along with a one-year follow-up. This process is then repeated in the second and third years. Eligible participants diagnosed with PAR were randomized at a ratio of 2 : 2 : 1 into one of three groups: (a) SHP group; (b) placebo group; or (c) waiting-list group. The waiting-list group will receive no treatment in the first year but will receive SHP in the following two years. The primary outcome, total nasal symptoms score, is self-assessed at the beginning of each treatment session and during each annual follow-up. Secondary outcomes include the Rhinoconjunctivitis Quality-of-Life Questionnaire, allergic rhinitis attacks, and relief medications. The trial will be stopped if early termination criteria are met during the interim analysis. *Ethics*. This protocol has been approved by site ethics committee (number B2014-014-01) and is registered with ClinicalTrials.gov NCT02192645.

## 1. Background

Allergic rhinitis (AR) is a common condition that affects 17–29% of the population of Europe [1–3] and 9–38% of the population of China [4]. AR can be subdivided into intermittent allergic rhinitis (IAR) or persistent allergic rhinitis (PAR) as described by the Allergic Rhinitis and its Impact on Asthma (ARIA) guidelines [1, 5]. Although not life-threatening, AR causes more than the classic symptoms. It also impairs sleep, work, or school performance, as well as several other domains of quality of life [6–8].

Currently, symptomatic pharmacotherapy used to treat AR includes antihistamines, intranasal corticosteroids, leukotriene receptor antagonists, and/or decongestants [9], but these treatments tend to cause undesirable side effects [5]. If AR patients fail to respond to the typical treatments, immunotherapy is considered. However, its anaphylactic risk, prolonged duration, and relatively high cost result in poor patient compliance. Consequently, complementary and alternative medicine treatments have been sought [10], especially traditional Chinese medicine (TCM) [11–13].

TCM management of health can be characterized as holistic with the emphasis on regulating the integrity of the human bodily functions and the interaction between individuals and their environments [14, 15]. According to TCM theory, patients with AR have insufficient* Yang Qi*, a metaphysical energy with a nature of hotness inside the body [16].* Sanfu* refers to the hottest period of the year, from July to August, and is considered to be the richest time for* Yang Qi* [16]. Therefore, the* Sanfu* period is of special significance for TCM in treating AR to gain more* Yang Qi* from the environment.

The Sanfu herbal patch (SHP) is a treatment method in which processed Chinese herbal preparations are applied directly to specific acupoints during the* Sanfu* period. This is done in order to produce therapeutic effects through the combination of herbal infiltration absorption, acupoint stimulation, and time effect [16]. The herbs with a nature of warm or hot are used to cause irritation on the skin such as local redness, hotness, and/or even blisters [17]. Therefore, skin absorption and stimulation of the meridians and/or acupoints are enhanced to generate a greater effect on patients. SHP was first applied to treat AR during the* Qing* dynasty (1644–1912) [18]. Nowadays, SHP has been awarded “Intangible Cultural Heritage” status in Guangdong province, China [19], and has achieved widespread popularity in mainland China [20]. In Beijing, there were 653 medical institutions using SHP in 2014 according to official data [21]. In addition, it was reported that the number of people receiving SHP in one TCM general hospital increased at an annual rate of 10% in recent years, to about 23,000 people in 2013 [22]. Due to the noninvasive and easy-to-manipulate nature of the treatment, SHP has also been increasingly used in TCM clinics in Taiwan [17, 23].

Several studies have been conducted to explore the efficacy of SHP for AR patients. Tai's observational study on SHP for patients who were diagnosed with allergic diseases indicated that SHP was effective among 60% of AR patients after treatment [17, 23]. However, patient-reported diagnosis of AR and uncertain criteria for determining treatment efficacy limit the interpretation of the results. Preclinical and clinical studies have shown that SHP is beneficial to AR via immunological mechanisms by decreasing the serum Immunoglobulin E (Ig E) [24–27]. Furthermore, a number of randomized controlled trials (RCTs) conducted in mainland China have demonstrated a promising effect of SHP in treating AR [28–43]. Three of them have observed a significant improvement in nasal symptoms and/or quality of life among patients receiving an SHP treatment, compared to those receiving a placebo [41–43]. In addition, an RCT conducted in Taiwan evaluated SHP versus a placebo and showed that SHP is effective, especially for nasal symptoms, and caused a significant improvement in patients' quality of life [28].

A recently published systematic review confirmed the effect of SHP. However, it also pointed out that previous RCTs have suffered from a variety of methodological limitations, including absence of sample size calculation, inappropriate control groups, and lack of clarity about the types of AR [20]. The Sanfu Herbal Patch Clinical Application Guidelines in China recommend three treatment sessions (TSs) per year for three consecutive years for treatment of AR [44]. However, most RCTs apply only three to five TSs, with or without a follow-up period [20]. A deficiency is evident even in a high-quality RCT [28] in which SHP was used for only 33 AR patients over an eight-week treatment period including six TSs. Furthermore, the outcome measurements were evaluated immediately after treatments at the 8th week, which could have produced bias without follow-up in AR high risk period. The safety issues of SHP could not be better addressed due to the short duration as well. This study also showed a significant improvement in nasal obstructions after treatment in the placebo group, which indicates a placebo effect (PE) in the treatment of AR. Therefore, a large-scale and rigorously designed RCT which overcomes identified methodological problems is necessary. The primary objective of this study is to evaluate the efficacy of SHP with a focus on the nasal symptoms in patients with PAR. Secondary objectives include an evaluation of whether SHP (1) can improve patients' quality of life, (2) can reduce the frequency of the allergic rhinitis attacks (ARAs), and (3) can alter the amount of relief medications (RMs) used. If the efficacy of SHP is confirmed, the PE of the SHP is further explored.

## 2. Methods

### 2.1. Design and Setting

This is a three-armed, randomized, and placebo-controlled trial, conducted in Guangdong Provincial Hospital of Chinese Medicine (GPHCM), Guangzhou, China. A flow chart of this trial is provided in Figure 1. The trial consists of 5 TSs conducted during the* Sanfu* period along with a one-year follow-up. This process is then repeated in the second and third years after treatment is begun. After providing written informed consent, eligible participants were randomized at a ratio of 2 : 2 : 1 into one of three groups: an SHP group receiving SHP treatment; a placebo group receiving placebo patch treatments; a waiting-list group receiving no treatment in the first year but then receiving SHP treatments the following two years. To allow for early termination, the trial will be assessed in two equally spaced interim analyses at the end of the first and second years, respectively. The trial will be stopped if a statistically significant difference between SHP and placebo is obtained during the interim analysis.

### 2.2. Participants

Participants were recruited via local advertising, local newspapers, and doctor referrals from otorhinolaryngology clinics in GPHCM. Interested individuals need to contact research assistants by phone or email. Trial information and consent forms were sent to them to read prior to scheduling their first visit. In the first visit, screening evaluations were conducted and recorded to ensure the eligibility of each individual. For each participant who was eligible and willing to participate in the trial, research assistants obtained a signed consent form.

For inclusion in this trial, participants had to meet the following criteria: aged ≥ 18 with PAR, defined clinically with symptoms being present at least 4 days a week, for at least 4 weeks [5]; having positive serum specific Ig E tests with results ≥ 0.35 IU/mL on mites (*Dermatophagoides pteronyssinus* or* Dermatophagoides farinae*), cockroach (*Blattella germanica*), or house dust; and having TNSS ≥ 3.

Main exclusion criteria for participants included one or more of the following: seasonal or chronic instance of other forms of rhinitis (i.e., sinusitis); asthma and/or moderate-to-severe atopic dermatitis; nasal structural abnormalities; diabetes mellitus requiring insulin injections; antiallergy treatment at present due to asthma, eczema, atopic dermatitis, or other diseases; serious acute or chronic organic disease or mental disorders; autoimmune disorders including the application of immunosuppressant or HIV infection; specific immunotherapy for >3 years; systemic corticosteroids treatment at time of treatment, or within the previous 6 months; intranasal corticosteroids at time of treatment, or within the previous 15 days; pregnancy or breast feeding; concurrent involvement in other clinical trials. Further exclusion criteria included blood coagulation dysfunction and/or use of antithrombotics at time of treatment and any TCM therapy such as acupuncture, moxibustion, and/or Chinese herbal medicine at time of treatment or within the previous month.

### 2.3. Randomization and Allocation Concealment

A block randomization sequence was generated by SAS 9.2 software (SAS Institute Inc., Cary, USA), which was performed by GPHCM's Key Unit of Methodology in Clinical Research (KUMCR). Eligible participants were randomly assigned to either the SHP group, the placebo group, or the waiting-list group at a ratio of 2 : 2 : 1. An independent researcher prepared treatment cards, on which a serial number and one of three names were printed, each representing one of the three groups. This person was also responsible for attaching a label including the name to the corresponding tube which was filled with either herbal or placebo ointment. Treatment allocations were stored in password-protected files and held independently by a staff of KUMCR. While receiving the first treatment, participants were given sequential treatment cards from independent researchers to ensure adequate concealment. Participants were then allocated into one of three groups according to the name printed on their treatment card. However, it was not possible to conceal the allocation among the waiting-list group.

### 2.4. Blinding

The participants, operational assistants, acupuncturists, research nurses, data managers, and statisticians do not know the treatment allocations, which will not be revealed until the end of study. However, blinding of the waiting-list group is not possible for this trial. For each participant, operational assistants prepare the patches by using ointment from tubes labeled with the same name as that on the participant's treatment card. The placebo patch is identical in appearance to the SHP. The implementation of treatments is performed by two acupuncturists using the patches prepared by the operational assistants. Due to the nature of SHP, it is difficult to ensure blinding among participants allocated to the SHP and placebo groups. Therefore, participants are required to wait for 60 minutes in a room, after which their treatment patches are torn off by research nurses. In addition, acupuncturists, operational assistants, and research nurses are instructed not to communicate with participants about the possibility of their allocation.

Participants from all three groups are instructed to stop symptomatic relief RMs during the one-week run-in and treatment periods. However, they are allowed to take RMs if needed during the follow-up period. These RMs are required to be documented in participants' diaries.

### 2.6. Outcome Measurement

For the evaluation of the primary and secondary outcome measures, participants are required to complete two questionnaires, the Total Nasal Symptom Score (TNSS) and the Rhinoconjunctivitis Quality-of-Life Questionnaire (RQLQ), at the beginning of each of five TSs (from 2nd to 7th weeks) and at the 8th, 19th, 33rd, and 52nd weeks during each annual follow-up. In addition, participants are asked to complete diaries throughout the trial. The frequency of the ARAs is recorded and the use of RMs or other medications is documented in detail (Figure 1).

The primary outcome is the change of the TNSS from baseline to the end of the 52nd week. TNSS evaluates four nasal symptoms: nasal obstruction, sneezing, rhinorrhea, and nasal itch. The symptoms are self-assessed and recorded by participants, using a five-point scale (0 = no symptoms; 1 = mild symptoms; 2 = moderate symptoms; 3 = severe symptoms; 4 = very severe symptoms) [45]. The TNSS ranges from 0 to 16, with low scores indicating lighter nasal symptoms.

Secondary outcomes include (1) the change of RQLQ score from baseline to the 8th, 19th, 33rd, and the 52nd weeks; (2) response to interventions, defined as participants with a change in RQLQ score of ≥0.5 from baseline; (3) the frequency of ARAs; and (4) the use of RMs. The PE of the SHP is further explored based on the TNSS and RQLQ score between the placebo group and the waiting-list group at the end of the 1st year.

### 2.7. Safety Assessment

An independent Data and Safety Monitoring Committee (DSMC) evaluates the progress of the trial and assesses the safety data which may be requested during the trial. Adverse events (AEs) are defined as any undesirable experience occurring to participants during the trial period, whether associated with the intervention or not. Participants are instructed to report any AE to the research team at any time. All details of AEs such as time of occurrence, severity, management, and causality to the intervention are recorded on case report forms (CRFs). The common AEs related to SHP include local itching, redness, and blisters [17]. The causality between AEs and intervention is assessed according to the WHO Uppsala Monitoring Centre System for Standardized Case Causality Assessment [46]. All AEs are followed up from the date they are brought to the investigator's attention until the AE has been resolved. Severe AEs or adverse drug reactions (ADRs) are defined according to the International Conference on Harmonization (ICH) guideline [47] and must be reported to both the DSMC and the Ethics Committee of GPHCM within 24 hours. In the event of an emergency medical situation, the individual's randomization code and group allocation can be identified via a standard operational procedure.

### 2.8. Quality Control

Before recruitment, the whole research team including acupuncturists, operational assistants, and research nurses were required to attend a training workshop. This was done before the trial to ensure their strict adherence to the study protocol and familiarity with the trial administration process. They are also provided with a written protocol and standard operation procedure documents. The two acupuncturists who apply the treatment each have acupuncture licenses from the Ministry of Health of the People's Republic of China and have over five years of experience in the application of SHP.

The data collected in this trial comprises information recorded in CRFs and information on the TNSS and RQLQ. Data is entered using the double-entry method. Data quality is checked regularly by research assistants and overseen by monitors. Data monitoring is conducted regularly with standard operation procedures by the Guangdong International Clinical Research Center of Chinese Medicine (Guangzhou, China). Audits are performed regularly by the GPHCM Department of Science Research. All modifications are marked on the CRFs. Data managers then recheck the data before logging it and promptly notify the research team if any discrepancy was found. The database is locked after all data has been cleaned. If participants withdraw from the trial either during the treatment period or the follow-up phase, the reasons should be clarified only if they are willing and the rate is analyzed via statistics.

### 2.9. Sample Size Calculation

We used a group sequential test to compare the SHP and placebo groups, hypothesizing a difference in the level of TNSS between SHP and the placebo. The sample size was calculated based on a mean change of 1.47 with a standard deviation (SD) of 2.9 scores in the SHP group and a mean change of 0.7 (SD: 1) scores in the placebo group [28]. We applied a 2 : 2 : 1 ratio to the SHP group, placebo group, and waitlist group, respectively. Considering a two-tailed significance level of 5% and a power of 80%, the sample size was 140 for the SHP group, 140 for the placebo group, and 70 for the waiting-list group. Assuming a dropout rate of approximately 20%, we will require a sample size of 174 for the SHP group, 174 for the placebo group, and 87 for the waiting-list group.

### 2.10. Statistical Analysis

Statistical analysis will be performed in a blinded manner by qualified statisticians using PASW Statistic 18.0 (IBM SPSS Inc., Armonk, New York, USA) and SAS 9.2 software (SAS Institute Inc., Cary, USA). Missing data will be replaced according to the principle of multiple imputations. Two-tailed *p* values < 0.05 are considered to be statistically significant. Analyses will be performed for 2 populations: (1) an intention-to-treat population with all patients randomized and treated with at least one TS and (2) a per-protocol population including only patients with no major protocol deviations.

Demographic and clinical characteristics, as well as baseline data, will be presented to assess the baseline comparability of the three groups. Descriptive statistics will be presented for each group as the mean change (SD, 95% confidence intervals) or the percentage change in the outcomes from baseline to each time point. Differences in mean change from baseline to each time point will be compared between groups using analysis of variance. Comparisons between the two groups will be conducted using the superiority test based on the Bonferroni adjustment. For the analysis of factors affecting the outcome change in each time point, mixed-effects linear or logistic regression model will be performed adjusting for baseline characteristics and other variables. Safety will be evaluated by tabulations of AEs and ADRs and will be presented with descriptive statistics for each group. A chi-square test or Fisher's exact test will be used to compare the frequency difference of AEs and ADRs among the three groups. As cases are divided into different degrees of AEs and ADRs, a rank-sum test will be performed for analyzing the independently ordered multiple category data among the three groups.

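### Change from baseline, the only between-group efficacy comparison described in section 2.10, suits relief-medication use and attack frequency poorly

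*Protocol article*

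**What the plan says.** Section 2.6 lists four secondary outcomes. The RQLQ outcome is defined as a change from baseline and the response outcome as a binary threshold on that change. The last two are listed only as "3) the frequency of ARAs; and (4) the use of RMs". Attacks and medication are taken from diaries kept throughout the trial.

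Section 2.10 then describes the outcomes by mean change, with its SD and 95% confidence interval, or by "the percentage change in the outcomes from baseline to each time point". The between-group test follows: "Differences in mean change from baseline to each time point will be compared between groups using analysis of variance". Two-group comparisons use a Bonferroni adjustment. The only other efficacy method there is a "mixed-effects linear or logistic regression model will be performed adjusting for baseline characteristics and other variables", offered for factors that affect the outcome change.

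Section 2.5 states: "Participants from all three groups are instructed to stop symptomatic relief RMs during the one-week run-in and treatment periods". Afterwards "they are allowed to take RMs if needed during the follow-up period", with use recorded in the diary.

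**The concern.** RM use and ARA frequency answer secondary objectives (2) and (3) in the Background. Both are diary quantities that accumulate over time, unlike a questionnaire score taken at a visit. A change score needs a baseline that carries information. For RM use, section 2.5 removes that information by design. For ARAs, the only scheduled pre-treatment period appears to be one week, because the run-in lasts one week and sessions begin in week 2. The follow-up visits at weeks 8, 19, 33 and 52 are separated by much longer intervals.

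At stake are one summary that cannot be calculated, a set of time points with nothing to compare, and avoidable loss of precision on attacks.

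**Working it through.** The plan gives no figure of its own for these two outcomes, so there is none to reproduce. From section 2.6, the intervals between follow-up visits are 19 − 8 = 11, 33 − 19 = 14 and 52 − 33 = 19 weeks, 44 in total. From section 2.9, the evaluable arms are 140, 140 and 70. Attack rates and their spread are not given and are assumed below.

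**Relief medication, for participants who follow section 2.5**

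- Baseline use B = 0. Percentage change = 100 × (F − 0)/0, which is undefined.
- Weeks 2 to 7: change = 0 − 0 = 0 in every arm. There is no variance between or within groups, so the ANOVA statistic is 0/0. Any non-zero value reflects a departure from the instruction.
- Follow-up: change = F − 0 = F. ANOVA on change is ANOVA on follow-up use. In 5,000 simulated null trials with arms of 140/140/70 and overdispersed counts, the two p-values were identical every time and the rejection rate was 5.5%.

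**Attacks, if the baseline is the one-week run-in**

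Let λ be the mean number of attacks per week, CV the between-person coefficient of variation of the rate, T the follow-up weeks, and k = λ·CV². Counts are taken as Poisson given each person's rate, which treatment leaves unchanged. B is the run-in count and F the follow-up rate per week.

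- Var(F) = λ(k + 1/T); Var(B) = λ(k + 1); Cov(F, B) = λk.
- Subtracting: Var(F − B) = λ(1 + 1/T).
- Adjusting linearly: Var(F) − Cov²/Var(B) = λ[k/(1 + k) + 1/T].
- Ignoring the baseline: λ(k + 1/T).

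With T = 19, so 1/T = 0.0526:

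| λ per week | CV | k | Subtract ÷ ignore | Subtract ÷ adjust |
|---|---|---|---|---|
| 1 | 0.5 | 0.25 | 1.0526/0.3026 = 3.48 | 1.0526/0.2526 = 4.17 |
| 1 | 0.7 | 0.49 | 1.0526/0.5426 = 1.94 | 1.0526/0.3815 = 2.76 |
| 1 | 1.0 | 1.00 | 1.0526/1.0526 = 1.00 | 1.0526/0.5526 = 1.90 |
| 1 | 1.5 | 2.25 | 1.0526/2.3026 = 0.46 | 1.0526/0.7449 = 1.41 |
| 5 | 0.5 | 1.25 | 1.0526/1.3026 = 0.81 | 1.0526/0.6082 = 1.73 |
| 5 | 1.5 | 11.25 | 1.0526/11.3026 = 0.09 | 1.0526/0.9710 = 1.08 |

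Subtracting may be better or worse than ignoring the run-in count. It is always less precise than adjusting for it, because k/(1 + k) is below 1.

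**Validity and power for attacks.** With a one-week baseline and a 44-week follow-up rate, ANOVA on change rejected 5.4% of null trials. With 140 per arm, a mean of 1 attack per week and a 20% reduction, the power of the change score was about 0.35 to 0.41 across CV 0.5 to 1.5. With the run-in count as a linear covariate it was 0.58 to 0.98.

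**Zero baselines for attacks.** At a mean of 1 per week, the share of participants with no run-in attack is e⁻¹ = 37% if everyone has the same rate, 1.25⁻⁴ = 41% at CV 0.5 and 2⁻¹ = 50% at CV 1 (gamma-distributed rates). Percentage change would be undefined for them too.

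**The case against.** The ANOVA sentence names no outcome and does not claim to cover all of them. Section 2.6 defines TNSS and RQLQ as changes but not ARAs or RMs, and the response outcome is binary, so a single rule cannot have been meant literally for everything. Percentage change is a descriptive alternative joined by *or*, perhaps meant for categorical outcomes, and no test uses it. A condensed article may also leave the model for diary counts to the full protocol or analysis plan.

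Much of this stands. The absence of a named count model is not an error in itself. What remains is that section 2.10 writes its rule for the outcomes generally, without exempting the two that it does not fit, and the conflict with section 2.5 is visible within the article.

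A reader might go further and infer that both analyses fail, or that the two objectives cannot be answered. The article does not support that: the follow-up RM test is an ordinary comparison of use, and the rejection rates under the null are close to 5%. A reader might also infer bias from the unequal intervals, since a raw count would rise 11- to 19-fold over a one-week baseline at a constant rate. But the article says frequency, which can be a rate, and all arms share the visit schedule, so interval length does not bias the randomised comparison. Only the descriptive change would mislead, and only if raw totals were used.

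**Conclusion.** The point holds as a limited one about suitability and precision.

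- For RM use, percentage change is undefined and change at weeks 2 to 7 is uninformative. Both rest on the run-in being the baseline and on participants complying. The follow-up comparison is valid but gains nothing from being called a change.
- For ARAs, subtracting a one-week count is unbiased but less precise than adjusting for it. The variance ratio is 1.4 to 4.2 at 1 attack per week and 1.1 to 1.7 at 5 per week, over CV 0.5 to 1.5. The one-week baseline is inferred from the run-in length, and the rates, CVs and Poisson form are assumptions. The loss is small if attacks are frequent and vary widely between people.

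The primary outcome is not affected. This is a cheap improvement to two secondary analyses.

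**What to change.** In section 2.10, limit change from baseline to TNSS and RQLQ. For the other two outcomes:

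- Compare RM use directly between groups over the follow-up diary weeks, as days of use per diary week and as the proportion with any use.
- Compare the ARA rate per diary week over the same weeks, using a rate or count model with log diary weeks as offset and the run-in ARA count as a covariate, not subtracted. State that the run-in is the baseline window, if it is. Attacks in the treatment weeks can be reported descriptively.
- Limit any comparison that treats the waiting-list group as untreated to year 1, since it receives SHP from year 2.

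The cost is revised wording, one further standard model and an assumption about the count distribution. The diaries already supply the data. The power figures above are for linear adjustment and would need a rerun for the count model chosen.

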The therapeutic effect of SHP integrates three main elements: herbal infiltration absorption, acupoints stimulation, and time effect [16, 51]. Generally, the herbal patches for allergic diseases are produced based on the Lengxiao formula, as recorded in the* Zhang Shi Yi Tong* (*Qing* dynasty) [52]. It consists of four herbs:* Semen sinapis*,* Herba asari*,* Radix kansui*, and* Rhizoma corydalis*. Although there are many variations in the prescriptions of the medicinal herbal patches in the treatment of AR, these four herbs are reported to be the most commonly used and primary components in SHP clinical trials [20]. The herbal patches in our trial also contain these four herbs as the main components and have been further developed by [name] who is a renowned acupuncture expert in China.* Ephedra sinica* is selected as one of the primary components because it is reported to have antiallergic effect in the experimental studies by inhibiting the release of allergic mediators [53] and vascular permeability [54]. This solution has been used to treat AR at GPHCM since the 1980s and has been reported to be effective for AR [55, 56] and asthma [57].

Local irritations caused by herbal patches not only make it easier for the body to absorb the medicinal substances through the skin but also enhance the stimulation of specific acupoints. Therefore, selections of acupoints could influence the effect of SHP. A review of clinical studies of SHP showed that most of the prescribed acupoints are located in the BL meridian on the back [58]; and BL12, BL13, BL20, and BL23 are the commonly selected acupoints. In this trial, most of the acupoints adopted in 2014 are located in the BL meridian and include these four acupoints (Table 1, Figure 2). We will not use the same acupoints for each year. This may influence the standardization for this trial. However, this reflects the actual treatment applied in the real practice.

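### The between-arm test on AEs and ADRs does not separate the skin reactions SHP is meant to cause, so a pooled result would say little about other harm

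*Protocol article*

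**What the plan says.** Four parts of the protocol article bear on this.

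- **Purpose of the irritation.** Section 1 (Background) says that the warm or hot herbs "are used to cause irritation on the skin such as local redness, hotness, and/or even blisters". Section 3 (Discussion) gives the reason: "Local irritations caused by herbal patches not only make it easier for the body to absorb the medicinal substances through the skin", and adds that the irritation strengthens acupoint stimulation.
- **Definition of an AE.** Section 2.7: "Adverse events (AEs) are defined as any undesirable experience occurring to participants during the trial period, whether associated with the intervention or not". Intended reactions are not excepted. The section continues: "The common AEs related to SHP include local itching, redness, and blisters".
- **Control arms.** Section 3 concedes that the placebo ointment resembles SHP in appearance but can hardly reproduce the skin reactions. Under section 2.5 the waiting list has no patch in year 1 and receives SHP in years 2 and 3.
- **Analysis.** Section 2.10: "Safety will be evaluated by tabulations of AEs and ADRs and will be presented with descriptive statistics for each group". Then a chi-square or Fisher's exact test "will be used to compare the frequency difference of AEs and ADRs among the three groups". For severity: "As cases are divided into different degrees of AEs and ADRs, a rank-sum test will be performed", again across the three groups. Degree is the only subdivision of events that it names.

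**The concern.** An effect that SHP is designed to produce is counted as an event in the safety test, and by the protocol's own account it will differ between arms. Equal AE frequency is therefore not a hypothesis anyone expects to hold, even if SHP does no other harm. A significant result could reflect nothing more than the expected redness. If it is explained that way, no stated between-arm test is left for other events.

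The other two stated tests do not repair this. Causality does not separate the two kinds of event, because intended irritation is itself treatment-related and so enters the ADR count. The rank-sum test orders events by degree rather than type, so redness and blisters feed into it as well.

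Safety is one of the trial's two headline aims (Abstract), and the protocol holds that the herbs are absorbed through the skin, so harm away from the application site is a fair question.

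**Working it through.** **The plan's own figure.** There is none for safety. The only design calculation (section 2.9) concerns TNSS and does not bear on this point. I take its randomized numbers, 174/174/87, and the two-sided 0.05 level of section 2.10 as given.

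**Assumptions.** The protocol states no AE rate, so every rate below is assumed. Let *o* be the proportion of participants with any other AE, equal in all arms unless stated. Let *i* be the proportion with a local reaction: varied for SHP, 5% for placebo, 0% for the waiting list (year 1 only). The two kinds of event are taken as independent, with one count per participant.

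**Formulas.** The proportion with any AE in an arm is p = 1 − (1 − o)(1 − i). Power of the three-group chi-square test comes from the noncentral chi-square with 2 df and λ = Σ n(p − p̄)² / [p̄(1 − p̄)], where p̄ is the pooled proportion.

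**Worked case, o = 10%, SHP i = 20%.**
- SHP: 1 − 0.90 × 0.80 = 0.280. Placebo: 1 − 0.90 × 0.95 = 0.145. Waiting list: 0.100.
- p̄ = (174 × 0.280 + 174 × 0.145 + 87 × 0.100)/435 = 82.65/435 = 0.190.
- λ = (174 × 0.0081 + 174 × 0.002025 + 87 × 0.0081)/(0.19 × 0.81) = 2.466/0.1539 = 16.0.
- Probability of rejection: 0.96.

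**Probability that the pooled test rejects when other AEs do not differ between arms**

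| SHP local reactions | other AEs 10% | 20% | 30% | 50% |
|---|---|---|---|---|
| 10% | 0.40 | 0.23 | 0.16 | 0.10 |
| 15% | 0.77 | 0.52 | 0.35 | 0.19 |
| 20% | 0.96 | 0.80 | 0.61 | 0.33 |
| 30% | >0.99 | 0.99 | 0.95 | 0.70 |

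With no local reactions on placebo and other AEs at 10%, the values are 0.67 at 10% SHP irritation and 0.995 at 20%.

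**Can the pooled test tell other harm from none?** Hold other AEs at 10% on placebo and waiting list. At 20% SHP irritation the test rejects with probability 0.80 if SHP halves other AEs (5%), 0.96 if they are equal, and above 0.99 if SHP doubles them (20%). At 30% irritation all three exceed 0.99.

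**ADRs.** If local reactions were the only ADRs, at 10% SHP, 5% placebo and 0% waiting list, then p̄ = 0.06, λ = 10.8 and the test rejects with probability 0.85.

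**Other AEs alone, SHP v placebo (1 df).** With equal rates the test rejects at its nominal 0.05. At 20% v 10%, p̄ = 0.15, λ = 348 × 0.05²/(0.15 × 0.85) = 6.82 and power is 0.74. The risk difference would be 10 points, with a 95% half-width of 1.96 × √[(0.20 × 0.80 + 0.10 × 0.90)/174] = 7.4 points.

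**The case against.** The strongest reply is that section 2.10 never uses the word total. The sentence follows one on tabulations, and testing each tabulated event type would fit the same words; the problem would then largely disappear. A breakdown by event type is also something an article may leave to the full protocol or SAP, so its absence alone is no defect. This stands as far as it goes. The point is confined to the test that the article names, on its most natural reading.

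A reader might infer that the test must reject by design. The documents do not support that. They give no irritation rate and say that skin reactions differ between individuals, and a false null does not make rejection certain. Section 2.7 counts unrelated events too, and the trial may run three years, so the background rate could well exceed 10%. The table shows how much that lowers the rejection rate.

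A reader might also infer that the trial cannot reveal other harm. That goes too far. Per-group tabulations, recorded severity and causality, expedited reporting and DSMC review can all bring non-local events to light. Nor is an excess that includes blisters meaningless, since blisters are a harm to the patient.

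Two further limits apply. The 0% waiting-list rate fits year 1 only. And no figure shows that local reactions would form most of the ADRs; the protocol says only that they are common.

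**Conclusion.** The point holds in a limited form. Run on all AEs combined, the stated three-group test is likely to be dominated by reactions that SHP is meant to cause, and it then says little about other harm. With other AEs at 10% in every arm and 5% local reactions on placebo, it rejects in about 40%, 96% and nearly 100% of trials at 10%, 20% and 30% SHP irritation. With other AEs at 30%, the figure at 20% irritation falls to about 61%.

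This rests on assumed rates, independence of local and other events, one count per participant, and year 1 conditions in the waiting list. Efficacy outcomes, sample size and stopping rule are unaffected. It is a cheap improvement to the safety comparison, not a flaw that invalidates the safety evaluation.

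**What to change.** In section 2.10:

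1. Report application-site reactions (redness, itching, blisters, pain or burning) separately, as participants affected in each arm, by degree.
2. Make the between-arm safety comparison all other AEs, and ADRs among them: participants affected, SHP v placebo, with the risk difference and its 95% confidence interval.
3. Keep overall AE and ADR totals as description.
4. Limit any three-group display to year 1, because the waiting list receives SHP from year 2.

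The cost is about two sentences, one derived yes/no field from AE details already on the CRF, and one more table. No new data or participants are needed. The drawback is that the comparison of other AEs rests on fewer events, so its interval is wider relative to the rates compared.
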